### **15.9 Recording and Reporting Urgent Safety Measures**

The Sponsor and investigator may take appropriate urgent safety measures to protect clinical trial subjects from any immediate hazard to their health and safety. The investigator may implement urgent safety measures without prior approval from the REC or MHRA.

When a PI becomes aware of information that necessitates an urgent safety measure, they should phone the MHRA Clinical Trials helpline on [name] and discuss the issue with a safety scientist or medical assessor immediately after an urgent safety measure has been implemented.

The PI or designee should report the urgent safety measure to the CTU immediately, using the dedicated email address [[contact]](mailto:[contact]).

The CTU will report the urgent safety measure to the Chief Investigator and to the Sponsor immediately, using the dedicated email address, [[contact]](mailto:[contact]).

The CI will notify the MHRA and the REC providing full details of the information they have received and the decision making process leading to the implementation of the urgent safety measure within 3 days.

The PI or designee should respond to queries from the Sponsor or Chief Investigator immediately to ensure the adherence to reporting requirements to REC and MHRA.

### **15.10 Pregnancy Reporting**

Pregnancy is not considered an AE or SAE, however an abnormal outcome would be. Therefore the PI or designee must collect pregnancy information for female participants, and for females who become pregnant while their partners are participating in the trial. Consent should be obtained to follow up the pregnancy from the female partners of male participants.

The pregnancy reporting period for the trial is from the commencement of the study drug until 28 days post study drug administration. The PI or designee should complete and submit the Pregnancy Reporting Form to the CTU by email ([[contact]](mailto:[contact])) within 14 days of being made aware of the pregnancy.

Any pregnancy that occurs in a participant or participant's partner during the reporting period should be followed to outcome. Follow up/outcome information should be provided to the CTU as soon as it becomes available.

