## 4 BACKGROUND AND RATIONALE

### 4.1 Acute Respiratory Distress Syndrome

Acute Respiratory Distress Syndrome (ARDS) is a common condition of acute hypoxemic respiratory failure resulting from disruption of the alveolar-capillary barrier, and a resultant inflammatory pulmonary oedema. It can occur in the critically ill in response to many insults including severe trauma, burns, infection, major surgery or neurological disorders. ARDS is a leading cause of death and disability in critically ill adults and children worldwide (1), with a hospital mortality of approximately 40% (1-3). UK data suggest that up to 20,000 cases of ARDS occur annually; 50% of these fall into the “moderate -severe” category of ARDS and have up to 40% mortality (2, 4). ARDS confers a considerable long-term illness and disability burden on the individual sufferer and on society. Only 50% of survivors are able to return to work 12 months after hospital discharge, while cognitive, psychologic, and physical morbidity persists for up to 5 years (5, 6).

ARDS has significant resource implications, prolonging intensive care unit (ICU) and hospital stay, and requiring rehabilitation in the community, all of which impact on NHS services. Patients with ARDS account for 10% of intensive care unit (ICU) admissions, and because they have a long average stay in ICU they use up to a quarter of ICU bed-days (7). The high incidence, mortality, long-term consequences and high economic costs make ARDS a major clinical problem. The estimated global annual cost of ARDS is \$613 million (USD). Within the NHS the estimated costs per patient up to 28 days are £22.5K and at 6 months are £30.5K (8).

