### Inclusion criteria

1. Moderate to severe ARDS as defined by the Berlin definition (62).
  - a) Onset within 1 week of identified insult
  - b) Within the same 24-hour time period
    - i. Hypoxic respiratory failure ( $\text{PaO}_2/\text{FiO}_2$  ratio  $\leq 27\text{kPa}$  on  $\text{PEEP} \geq 5\text{ cmH}_2\text{O}$ )
    - ii. Bilateral infiltrates on chest X-ray consistent with pulmonary oedema not explained by another pulmonary pathology
    - iii. Respiratory failure not fully explained by cardiac failure or fluid overloadThe time of onset of ARDS is when the last ARDS criterion is met.
2. Patient is receiving invasive mechanical ventilation.
3. COVID-19 based on clinical diagnosis or PCR test or other cause of ARDS.

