### Exclusion criteria

1. More than 72 hours from the onset of ARDS.
2. Age  $< 16$  years.
3. Patient is known to be pregnant.
4. Major trauma in the prior 5 days.
5. Presence of any active malignancy (other than non-melanoma skin cancer) that required treatment within the last year.
6. WHO Class III or IV pulmonary hypertension.
7. Venous thromboembolism currently receiving anti-coagulation or within the past 3 months.
8. Currently receiving extracorporeal life support (ECLS).
9. Severe chronic liver disease with Child-Pugh score  $> 12$ .
10. DNAR (Do Not Attempt Resuscitation) order in place.
11. Treatment withdrawal imminent within 24 hours.
12. Consent declined.

13. Prisoners.
14. Non-English speaking patients or those who do not adequately understand verbal or written information unless an interpreter is available.
15. Previously enrolled in the REALIST trial.

Our inclusion and exclusion criteria are designed to include those who reflect the general population of critically ill patients with ARDS due to COVID-19 or other causes of ARDS who may benefit from the therapeutic intervention and exclude patients who may be more likely to experience an adverse reaction.

A pregnancy test in females with child bearing potential (aged 15-55 years) will be performed prior to enrolment and patients who are pregnant will be excluded. Given the population being recruited is critically ill the need for contraception advice is recognised to be very unlikely. At the discretion of the investigator, contraception advice will be given to patients at hospital discharge who may be sexually active prior to day 90.

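### Section 15.10 ends the pregnancy reporting period, and the outcome follow-up tied to it, at day 28, while contraception advice (8.3) and adverse event reporting (15.7) look to day 90

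*Protocol*

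**What the plan says.** Section 15.10 has three parts that bear on this.

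- The first paragraph says that pregnancy is not itself an adverse event but an abnormal outcome would be. On that basis it obliges the site to collect pregnancy information for female participants and "for females who become pregnant while their partners are participating in the trial". It gives no day limit.
- The second paragraph sets the period: "The pregnancy reporting period for the trial is from the commencement of the study drug until 28 days post study drug administration". The reporting form is due "within 14 days of being made aware of the pregnancy".
- The third paragraph ties outcome follow-up to that period: a pregnancy in a participant or partner "during the reporting period should be followed to outcome".

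Other sections use a longer horizon. The text after the exclusion criteria in section 8.3 says that, at the investigator's discretion, "contraception advice will be given to patients at hospital discharge who may be sexually active prior to day 90". It also says that contraception advice will very rarely be needed. Sections 12.2 and 15.7 run adverse event collection to day 90.

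**The concern.** The 28-day period covers the weeks when conception is least plausible. Every participant meets the inclusion criterion "Patient is receiving invasive mechanical ventilation", and section 4.1 says that patients with ARDS use many ICU bed-days "because they have a long average stay in ICU". For many survivors the period will therefore end at about the time they go home. The days left out, 29 to 90, are mainly the post-discharge time that section 8.3 has in mind when it offers contraception advice.

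At stake is a small piece of safety information on a cell product that, according to section 15.6, had not previously been given to patients with ARDS. If a participant or partner conceives on days 29 to 90, the protocol does not say that the pregnancy is followed to its outcome, and it leaves unclear whether the pregnancy form is due.

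**Working it through.** The protocol gives no figure to reproduce here, so the check compares the windows and then sizes the gap.

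**1. The windows, counted from study drug**

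| Item | Section | Ends |
|---|---|---|
| Pregnancy reporting period | 15.10, second paragraph | day 28 |
| Outcome follow-up of pregnancies | 15.10, third paragraph | no end date, but only for pregnancies occurring by day 28 |
| Duty to collect pregnancy information | 15.10, first paragraph | no day stated; for partners, while the patient is participating |
| Contraception advice at discharge | 8.3 | day 90 |
| Adverse event reporting | 12.2, 15.7 | day 90 |

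The period is defined by when the pregnancy occurs. A conception by day 28 that is discovered later is therefore still covered, and the gap concerns conceptions on days 29 to 90.

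**2. Other routes for a pregnancy conceived on days 29 to 90**

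- *Participant:* an abnormal outcome by day 90 is an adverse event (15.7, 15.10). A serious event at least possibly related to study drug is reported whenever the investigator becomes aware of it (15.8), and congenital anomaly is one of the seriousness criteria (Table 3). Significant medical events are collected at years 1 and 2 (12.4).
- *Partner:* Table 3 defines an adverse event as occurring in a participant who received the product, and 12.4 collects participants' events. These routes do not clearly reach a partner. Because 15.10 gives the abnormal-outcome rule as its reason for collecting partner pregnancies, a route is arguable, but none is spelled out.

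**3. Size in calendar time**

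Share of the 90-day horizon outside the period: (90 − 28)/90 = 62/90 = 68.9%. This is a share of days, not of risk.

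The protocol gives no typical discharge day. For an assumed hospital discharge on day d, the share of post-discharge days to day 90 that falls outside the period is 62/(90 − d):

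- d = 14: 62/76 = 81.6%
- d = 21: 62/69 = 89.9%
- d = 28: 62/62 = 100%

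**4. Size in expected events**

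Inputs from the protocol: 60 + 60 = 120 phase 2 patients (14.1) and hospital mortality of about 40% (4.1), which leaves 120 × 0.60 = 72 survivors. Assumed inputs: 5% to 20% of survivors have reproductive potential, their own or through a partner, and 2% to 8% of these conceive per year.

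- Low: 72 × 0.05 × 0.02 × 62/365 = 0.012
- High: 72 × 0.20 × 0.08 × 62/365 = 0.196

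Chance of at least one (Poisson): 1 − exp(−0.012) = 1.2%, and 1 − exp(−0.196) = 17.8%. The calculation treats every survivor as at home for all of days 29 to 90. Some will be discharged later, so it errs high.

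**The case against.** The strongest reply is that 15.10 opens with a mandatory collection duty without a day limit, and that patients participate for up to two years. On that reading, information on a pregnancy at day 60 must be collected, and the 28-day period limits only the form and the outcome follow-up. This stands. A reader might infer from the second paragraph that nothing has to be reported after day 28, but the document does not support that: the first paragraph is undated, nothing in the section says that the second paragraph caps it, and 15.8 adds an undated duty for possibly related serious events. What the reply does not supply is outcome follow-up, which the third paragraph attaches expressly to the reporting period.

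A second reply is that the windows need not match. A reader might see a contradiction between day 28 and day 90, but there is none: pregnancy is not an adverse event, and the two periods serve different purposes. Nor does the protocol present day 90 as a period of reproductive risk after a single infusion. It appears in a sentence about discretionary advice whose need is described as remote. The document therefore does not show that 28 days is too short biologically. It shows only that 28 days sits poorly with the horizon the protocol uses when it considers conception after discharge.

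A third reply is that the yield is almost nil and that the sizing rests on assumed inputs. Both are true, and they determine the priority.

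**Conclusion.** The point holds as a cheap, low-priority improvement. Section 15.10 leaves a pregnancy conceived on days 29 to 90 without stated outcome follow-up and leaves its collection ambiguous. Participants have partial back-up through the adverse event rules and the annual follow-up, so the gap is clearest for partners.

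The size is small: an expected 0.01 to 0.20 conceptions in the uncovered days, with zero the most likely count. That range depends on the assumed reproductive potential and conception rate and on the protocol's mortality figure. The statement that the period falls largely in ICU or hospital time is an inference from ventilation at entry and the general remark on ICU stay, since no discharge data are given. Neither the sample size nor any efficacy conclusion is affected.

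**What to change.** In the second paragraph of 15.10, change the end of the pregnancy reporting period from 28 to 90 days after study drug administration. Pregnancies arising to day 90 then use the existing form and its 14-day deadline, and the third paragraph carries them to outcome without further editing. Leave the first paragraph's collection duty as it is: tying it to the reporting period would narrow a duty that currently has no day limit.

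The cost is one changed number at the next amendment and, rarely, an extra pregnancy to follow and a partner's consent to obtain, both of which 15.10 already provides for. Reporting would still depend on the site becoming aware. For discharged patients, section 12.4 describes only mortality collection at day 90, so without an active question some pregnancies may still go unnoticed.

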## **16 DATA MONITORING**

### **16.1 Data Access**

The agreement with each PI will include permission for trial related monitoring, audits, ethics committee review and regulatory inspections, by providing direct access to source data and

trial related documentation. Agreement/consent from patients/Personal Legal Representative/Professional Legal Representative as appropriate for this will also be obtained. The patient's confidentiality will be maintained and will not be made publicly available to the extent permitted by the applicable laws and regulations.

## **16.2 Monitoring Arrangement**

The CTU will be responsible for trial monitoring. On-site monitoring visits will be conducted in accordance with the trial monitoring plan. The frequency and type of monitoring will be detailed in the monitoring plan and agreed by the trial Sponsor.

Before the trial starts at a participating site, an initiation "visit" will take place to ensure that site staff are fully aware of the trial protocol and procedures. Given the impact of the COVID-19 pandemic on, for example, travel and access to sites, these "visits" might take place remotely. Checks will take place to ensure all relevant essential documents and trial supplies are in place. Monitoring during the trial will check the accuracy of data entered into the CRF against source documents, adherence to the protocol, procedures and GCP, and the progress of patient recruitment and follow up.

The PI or designee should ensure that access to all trial related documents including source documents are available during monitoring visits. The extent of source data verification (SDV) will be documented in the monitoring plan.

## **17 REGULATIONS, ETHICS AND GOVERNANCE**

The trial will comply with the principles of GCP, the requirements and standards set out in the Research Governance Framework and the Medicines for Human Use (Clinical Trials) Regulations 2004 and subsequent amendments, and any new relevant legislation or regulations introduced because of the COVID-19 pandemic.

### **17.1 Regulatory and Ethical Approvals**

The trial will be conducted in accordance with the ethical principles that have their origin in the Declaration of Helsinki. The protocol will be approved by a Research Ethics Committee (REC). A clinical trial authorisation (CTA) will be obtained from the Medicines for Healthcare products Regulatory Agency (MHRA) before the start of the trial.

The trial protocol was prepared in compliance with the SPIRIT 2013 statement (72). The trial will be registered at [www.clinicaltrials.gov](http://www.clinicaltrials.gov) and the European Union Drug Regulating Authorities Clinical Trials (EudraCT) database.

### **17.2 Ethical Considerations**

The vulnerability of this study group is fully appreciated and every effort will be undertaken to protect their safety and well-being, in line with The Medicines For Human Use (Clinical Trials) Regulations 2004 and subsequent amendments and the Research Governance Framework.

### **17.3 Protocol Compliance**

The investigators will conduct the study in compliance with the protocol given approval/favourable opinion by the REC and the MHRA.

A protocol deviation is defined as an incident which deviates from the normal expectation of a particular part of the trial process. Any deviations from the protocol will be fully documented on the protocol deviation form in the CRF.

A serious breach is defined as a deviation from the trial protocol or GCP which is likely to effect to a significant degree:

- (a) the safety or physical or mental integrity of the subjects of the trial; or
- (b) the scientific value of the trial

The PI or designee is responsible for ensuring that any potential serious breaches are reported directly to the CTU within one working day using the dedicated email address [[contact]](mailto:[contact]). The CTU will notify the CI and Sponsor immediately to ensure the adherence to reporting requirements to REC and MHRA where a serious breach has occurred.

Protocol compliance will be monitored by the CTU who will undertake site visits to ensure that the trial protocol is adhered to and that necessary paperwork (e.g. CRF's, patient consent) is being completed appropriately.

#### **17.4 Protocol Amendments**

All protocol amendments will be undertaken in accordance with the regulatory requirements. Substantial changes to the protocol will require REC and MHRA approval prior to implementation, except when modification is needed to eliminate an immediate hazard(s) to patients.

#### **17.5 Good Clinical Practice**

The trial will be carried out in accordance with the principles of the International Conference on Harmonisation Good Clinical Practice (ICH-GCP) guidelines ([www.ich.org](http://www.ich.org)). All members of the trial team will be required to have completed GCP training.

#### **17.6 Indemnity**

The BHSCIT will provide indemnity for any negligent harm caused to patients through the Clinical Negligence Fund in Northern Ireland. QUB will provide indemnity for negligent and non-negligent harm caused to patients by the design of the research protocol.

#### **17.7 Patient Confidentiality**

In order to maintain confidentiality, all CRFs, questionnaires, study reports and communication regarding the study will identify the patients by their unique participant study number and initials only. Patient confidentiality will be maintained at every stage and will not be made publicly available to the extent permitted by the applicable laws and regulations.

#### **17.8 Data Access**

All essential documentation i.e. the Investigator Site file (ISF) and source data will be stored by sites. The TMF and associated trial data will be stored by the CTU in conformance with the applicable regulatory requirements and access to stored information will be restricted to authorised personnel. Following the publication of the primary and secondary study outcomes, there may be scope to conduct additional analyses on the data collected. In the event of publications arising from such analyses, those responsible will need to provide the CI with a copy of any intended manuscript for approval prior to submission.

## 17.9 Record Retention

The site PI will be provided with an ISF by the CTU and will maintain all trial records according to GCP and the applicable regulatory requirements. The PI is responsible for the archiving of essential documents at local sites in accordance with the requirements of the applicable regulatory requirements, Sponsor and local policies. The PI has a responsibility to allow Sponsor access to archived data and can be audited by the Sponsor on request. Following confirmation from the Sponsor the CTU will notify the PI when they are no longer required to maintain the files. If the PI withdraws from the responsibility of keeping the trial records, custody must be transferred to a person willing to accept responsibility and this must be documented in writing to the CTU and Sponsor.

The TMF will be held by the CTU within the BHSCT and the essential documents that make up the TMF will be listed in a SOP. On completion of the trial, the TMF and study data will be archived by the CTU according to the applicable regulatory requirements and as required by the BHSCT as Sponsor.

## 17.10 Competing Interests

The research costs including the cost of the intervention are funded by the Wellcome Trust and the Research and Development Division of the Public Health Agency, Northern Ireland. The CI and members of the TMG have no financial or non-financial competing interests and the members of the DMEC/TSC will be asked to confirm that they have no conflict of interest. In the event that a DMEC/TSC member reports a conflict of interest, advice will be sought from the Sponsor.

# 18 DISSEMINATION/PUBLICATIONS

## 18.1 Publication Policy

The trial will be reported in accordance with the Consolidated Standards of Reporting Trials (CONSORT) guidelines ([www.consort-statement.org](http://www.consort-statement.org)).

We plan to publish our trial protocol and statistical analysis plan to ensure transparency in our methodology. The phase 1 will be published on completion. Data from each cohort in the phase 2 trial will be published when data on the primary outcome is available and in keeping with best practice. Long term data and mechanistic data will also be reported although may form the basis of separate publications.

The study findings will be presented at national and international meetings with abstracts on-line. Presentation at these meetings will ensure that results and any implications quickly reach all of the UK intensive care community. This will be facilitated by our investigator group, which includes individuals in executive positions in the UK Intensive Care Society. We will comply with the Wellcome Trust open access policy and publish the findings of the trial in peer-reviewed open access (via Pubmed) journals. This will secure a searchable compendium of these publications and make the results readily accessible to the public, health care professionals and scientists. Any rapid dissemination methods available for COVID-19 trials will be used.

A lay person's summary of the principal findings of the results will be sent to all patients involved in the study at their request. The most significant results will be communicated to the

public through press releases. An on-going update of the trial will also be provided on the CTU website.

## **18.2 Authorship Policy**

Authorship will be determined according to the internationally agreed criteria for authorship ([www.icmje.org](http://www.icmje.org)).

